#### Plans to promote participant retention and complete follow-up {18b}

To promote retention, feedback on measured outcomes will be provided and patient education and self-management materials regarding CLBP will be distributed. In addition, all participants will be thanked for their participation and reminded of their progress in the study, upcoming data collection, and contribution to the study results. The protocol will take a flexible approach to the study schedule, and every effort will be made to resolve any conflicts that may arise. Moreover, family support will be sought, and participants will be taught to incorporate treatment into their daily life.

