**Methods:**

The trial is a randomized, controlled, multi-center study with four experimental groups and one healthy control group. Both the researchers and the people in the study will be blinded to the results. This paper describes the protocol for a trial examining the effects of 12-week individualized, twice-weekly exercise sessions lasting 30 to 60 min in persons with CLBP, who are positive for CS. Participants will be randomized to receive either patient education with motor control exercises (MCE), superficial strengthening (SS), aerobic exercises (AE), or patient education alone. Another group comprised of healthy volunteers will serve as controls. The primary outcomes are changes in CPM outcomes as measured by the cold pressor test (CPT). The secondary objectives are to evaluate executive functioning, pain, disability, quality of life, and spine muscle strength. The outcomes will be measured at 3 months and at a 6-month follow-up.

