### Trial design {8}

This is a randomized, controlled, double-blinded study determining how CPM changes in response to three types of active exercises in CS-positive CLBP patients. Participants will be randomized to undergo 12 weeks of the motor control exercise (MCE), superficial strengthening (SS), or AE combined with patient education or patient education alone. This active treatment concurrent control design will be used to demonstrate superiority of one exercise group over another. All patients will be allocated in a 1:1:1:1 ratio using random number tables. All participants will receive advice to stay active. Another no-pain control group will also be recruited. The intervention will be provided for 12 weeks. An independent assessor will collect data at baseline (t0), after intervention at 3 months (t1), and at the 6-month follow-up (t2). Outcome measures include CPT for measuring CPM, letter–number sequencing subtest in the Wechsler Adult Intelligence Scale-III Edition (WAIS-III), Stroop neurophysiological test, QoL assessed using the abbreviated WHOQOL-BREF questionnaire, isometric muscle strength of spine and hip muscles, the Oswestry Disability Index (ODI) questionnaire, and the Numerical Pain Rating Scale (NPRS). Table 1 and Fig. 1 present the study design and flowchart, respectively. The research ethics approval was granted by the Integral University, India (IIAHSR/DO/PT/2022/23), and Composite Regional Centre for Skill Development, Rehabilitation, and Empowerment of Persons with Disabilities, India (CRCL/Ph.D. Data Collection/2021–22/1556). The study is designed according to the Consolidated Standards of Reporting Trials (CONSORT) guidelines and reported according to the Standard Protocol Items: Recommendations for Interventional Trials (SPIRIT) checklist. The study will use a 5 (between subjects − type of exercise interventions: MCE vs. AE vs. SS vs. patient education vs. no-pain control) × 3 (within subjects − time: before vs. after vs. 3 months after the intervention) mixed design.

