### Assignment of interventions: blinding

#### Who will be blinded {17a}

The present study is designed as a randomized controlled trial. The intervention groups will be blinded from one another and outcome assessors. All outcome measures will be determined by an independent researcher blinded to treatment allocation. The assessor will attend training sessions on assessment procedures where the proposed assessment methods will be discussed in detail. The participants will be instructed to not disclose their intervention allocation to the outcome assessor. They will be informed that the effect of different active exercise programs will be evaluated so that they are unaware of any expected treatment group benefit. Another experienced researcher will feed the collected data into the computer. The researcher conducting the statistical analysis will not be present when the measurements are taken. All physiotherapists providing interventions will be blinded to the results of evaluations, measurements, and questionnaires.

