#### Procedure for unblinding if needed {17b}

Complete blinding of investigators and participants will be attempted. The actual allocation will not be disclosed to members outside the research team. Unmasking will be permitted only under special circumstances in which knowledge of the allocated treatment is necessary for further patient care. The primary investigator will take decisions regarding unblinding in consultation with a physician.

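### Feedback on measured outcomes, given to aid retention, conflicts with the statement that participants are blinded to the results and could influence the participant-reported 6-month outcomes

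*Protocol article*

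**What the plan says.** **Retention.** Section {18b} states, with retention as the declared purpose, that "feedback on measured outcomes will be provided". It adds that participants will be thanked and "reminded of their progress in the study, upcoming data collection, and contribution to the study results". It does not say when the feedback is given, what it contains or who gives it.

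**Blinding.** The Abstract, under Methods, states: "Both the researchers and the people in the study will be blinded to the results". Section {17b} says: "Complete blinding of investigators and participants will be attempted". Section {17a} describes how the trial is presented to participants, "so that they are unaware of any expected treatment group benefit", and separately states: "All physiotherapists providing interventions will be blinded to the results of evaluations, measurements, and questionnaires".

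**Timing of outcomes.** Section {8} sets three assessments: baseline (t0), 3 months (t1) and 6 months (t2). Section {12} defines the primary endpoint through the PPT change in the cold pressor test and the NPRS change to week 12. It places the ODI and WHOQOL-BREF, among others, at weeks 12 and 24. Section {20a,b} analyses CPM, pain, disability and quality of life over all three times, and makes clinical significance depend on the 10% PPT change persisting to 6 months.

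**The concern.** A trial that says its participants are blinded to the results should not also report results to them while outcomes are still being collected. The outcomes at stake are ones the participant supplies. A person told at 3 months that the pain threshold response or disability score has moved, or has not, may answer differently at 6 months for reasons unrelated to the exercise programme.

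The 6-month visit carries weight here because it decides whether the CPM change counts as clinically significant. If knowledge of t1 results shifts the t2 response, the trial cannot separate a maintained effect of exercise from a reaction to the feedback.

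**Working it through.** No figure in the protocol bears on the size of this effect, so the check sets the sections side by side.

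**1. Do the statements conflict?** The answer depends on what the Abstract means by results. Section {17a} uses the word for evaluations, measurements and questionnaires, which are individual data. On that reading, participants cannot be blinded to results and also receive feedback on measured outcomes. If the Abstract means only comparative trial results, the literal conflict goes, but the exposure in steps 2 to 4 remains.

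**2. When would the feedback come?** Its stated purpose is retention, under a heading that also names complete follow-up. The natural reading is that it is given while there are still visits to retain people for, that is, before t2. No other section postpones it.

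**3. Which outcomes could it reach?** The scheduled sequence is t0, then t1, then t2.

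| Interval | What feedback could contain | Outcomes collected next |
|---|---|---|
| t0 to t1 | Baseline values only; no change yet measured | Week-12 outcomes |
| t1 to t2 | Change from baseline to t1 | 6-month outcomes |
| After t2 | Everything | None |

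Before t1, the content could be baseline values. Randomisation makes these alike across the randomised arms in expectation, so the week-12 comparison between arms is largely unaffected. It is not wholly closed off: {12} refers to an average daily NPRS score and {22} has changes in pain and CPM recorded for safety, so some interim information may exist.

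After t1, the content can be the participant's own change. The t2 outcomes that rest on the participant's report are:

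- PPT, and so CPM: the reading is taken when the participant says that pressure has become pain.
- NPRS: a self-rating, collected at t2 under {8}.
- ODI and WHOQOL-BREF: questionnaires, with week 24 named in {12}.

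**4. Would it cancel between arms?** Section {18b} does not restrict feedback to any arm, so the offer is the same for all. The content is not fixed, because it follows each person's t1 results. If the arms do not differ at t1, the content is alike on average and no systematic difference need follow. If they do differ, the content differs by arm, and randomisation does not balance what happens after it. Good news could sustain a response or raise expectations that are then disappointed, so the direction cannot be stated.

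**5. What is the retention stake?** Section {14} plans for 30 evaluable participants per group and 30% dropout: 30 / (1 − 0.30) = 42.9, rounded up to 43, as stated. The plan therefore allows for 43 − 30 = 13 losses per group. Retention is a real concern, and the fix should preserve as much of the incentive as it can.

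**The case against.** The strongest reply is that the conflict rests on one loose sentence in the Abstract. Participants fill in the NPRS, ODI and WHOQOL-BREF themselves, so they cannot literally be blinded to those answers. The operative section, {17a}, asks only that they not know which group is expected to benefit, and {17b} is about allocation. A person's own scores reveal neither. Section {18b} also gives no timing, and a promise of feedback at the end can itself encourage people to stay.

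Much of this stands. The point is not that allocation is unmasked. The timing is inferred from the purpose of the feedback, although the inference is the natural one. But knowing one's own answers is not the same as being told a computed change or a CPM result, which a participant would not otherwise have. The article should say which kind of blinding it means.

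A reader might go further in four ways that the document does not support:

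- **That therapist blinding is contradicted.** Section {18b} does not say that physiotherapists give or receive the feedback. Participants might mention their results in sessions, but that exposure is indirect.
- **That the progress reminder is also outcome feedback.** It stands beside upcoming data collection and may mean progress through the schedule. The firm evidence is the feedback sentence alone.
- **That every self-reported outcome is decided at 6 months.** Section {20a,b} attaches 6 months only to the PPT change. Its thresholds for the NPRS, ODI and WHOQOL-BREF carry no such condition.
- **That arm differences at 6 months will be inflated by some number of points or kPa.** The document supports neither the direction nor any magnitude.

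**Conclusion.** The concern holds in a limited form. As written, {18b} and the Abstract conflict, and following {18b} could let participants know their t1 results before giving participant-reported outcomes at t2. The most consequential of these is the PPT-based CPM measure, because of the 6-month condition in {20a,b}.

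This rests on two readings: that results in the Abstract include the participant's own, and that retention feedback comes before the last visit. Both are the more natural reading, and nothing in the article contradicts them. The size of any bias is not estimable from the document. The planned power and sample size are not in question on this point. The correction is worth making because it is cheap and the t2 outcomes cannot be protected afterwards.

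**What to change.** In section {18b}, state that individual outcome feedback is released only after the participant's t2 assessment. Keep all the other retention measures: thanks, reminders of the schedule and of upcoming data collection, education and self-management materials, flexible scheduling and family support. If the progress reminder means progress through the schedule, say so.

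In the Abstract, state what participants are blinded to, for example their own outcome results until after t2, the expected benefit of each group, or both, and make {17a} consistent with it.

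The cost is about one sentence in each place and the loss of one retention incentive before t2. Part of that incentive survives, since participants can be promised their results at the end of the study. With 30% dropout anticipated, the trade-off should be acknowledged; the document gives no figure for how much this one measure contributes to retention.

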#### Data management {19, 27}

Participants’ personal information and confidentiality will be protected during all trial phases. All participant data including all reports, data collection, process, and administrative forms will be housed in lockable file cabinets in restricted-access zones and shall be identifiable solely by a coded ID [identification] number. The participant’s unique number identifier, and not their names, will be displayed in all the data. Forms, lists, logbooks, appointment books, and any other listings that link participant ID numbers to other identifying information will be kept in a closed, separate file in a restricted area. Only the primary investigator will know the name associated with the number. All data collected will be converted into the electronic format and will be stored in password-protected files in a secure place at the main study centers from where the data were collected. The data will be accessible to only the research team. All personal data will be stored separately from other data and treated as confidential, will be accessible to only selected research team members, and will not be shared. The data will be retained for 5 years after study completion. Without the participant’s explicit consent, the participant’s study information will not be disclosed outside of the study.

### Statistical methods

#### Statistical methods for primary and secondary outcomes {20a,b}

The Shapiro–Wilk test will be used to assess the normality of the distribution of the data. A one-way analysis of variance (ANOVA) will be used to compare baseline characteristics between the groups. Descriptive statistics will be used to calculate the mean values of all outcome variables collected. A repeated measure ANOVA statistic will be used to evaluate the effect of three types of exercise interventions on CPM, neurophysiological outcomes, pain, disability, strength measures, and QoL. The study will use a 5 (between subjects – type of exercise interventions: AE vs. MCE vs. SS vs. patient education vs. no-pain control) × 3 (within subjects – time: before vs. after vs. 3 months after the intervention) mixed design. Tukey’s post hoc analysis will be conducted to establish differences between the groups. Effect size will be estimated by dividing the mean difference in outcomes between the intervention and control groups by the combined standard deviation of the two groups [56].

The primary outcome will undergo a per-protocol analysis. Pearson correlation analysis will be performed to determine the relationship between patient characteristics (Table 4), CPM, executive functioning, pain, strength measures, disability, and QoL. Multiple linear regression analysis will be used to deduce the characteristics of individuals responding positively to exercise interventions. For all measurements, *p* will be considered significant, if it is < 0.05. The data collected will be analyzed using SPSS (Statistical Program for the Social Sciences) 16.0 (IBM Corp., Armonk, NY).

**Table 4 Tab4:** Summary of patient characteristics to be collected

Characteristics	CLBP group	Control group
Age (years)	X	X
Gender (male/female)	X	X
Pain episode duration (weeks)	X	X
Body mass index (kg/m^2^)	X	X
Education level (yes/no; school incomplete, completed secondary school, completed diploma/completed bachelors and above)	X	X
Employment status (yes/no; employed (full or part-time), unemployed, retired)	X	X
Marital status (yes/no; married/separated/ divorced, single)	X	X
Personal behaviors Alcohol status (yes/no) Smoking status (yes/no)	X	X
Comorbidities	X	X
Fear avoidance behavior	X	X
Perception of improvement	X	X

The results will be considered clinically significant if a minimum difference of 10% change in PPT values in CPT is maintained at 6 months. Based on a previous study results [57] and a standardized mean score of 10 [58] on the letter–number sequencing subtask of WAIS-III, the mean reaction time for the Stroop interference effect will be fixed at approximately 230 s for the treatment to be considered successful. A reduction of 2 points on the NPRS [59], a cut-off value of 13, and a difference of 8 and 4 points will be considered as the minimal clinically important difference for the ODI [60], WHOQOL-BREF [61], and isometric muscle strength [62] respectively, which would indicate the success of the therapeutic intervention used.

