#### Outcomes {12}

The primary efficacy endpoint will be a minimum difference of 10% change in PPT values in CPT and a difference of ≥ 20% from baseline to week 12 in the average daily score on an 11-point (0–10) NPRS. Secondary endpoints include change from baseline to weeks 12 and 24 in number sequencing subtest, Stroop neurophysiological test, isometric muscle strength of spine and hip muscles, and the WHOQOL-BREF and ODI questionnaires.

All outcome measures will be administered or translated into Hindi for those who have difficulties reading, comprehending, and understanding English. All translations will conform to the standard guidelines for translation of patient-reported outcome measures [40].

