### Primary outcome measure

#### CPM

The CPT will be used to measure CPM. For the conditioning stimulus, the participants’ non-dominant hand will be immersed in a bucket with temperature-controlled cold water (1 °C–4 °C), monitored by a thermometer for up to 1 min. The participant has to remain with the hand immersed in water without making muscle contractions or changes in position. Withdrawal from the water will be allowed if the patient can no longer tolerate the painful stimulus. This test will be conducted in a room with controlled room temperature, humidity, lighting, and noise.

Using a digital pressure algometer, the pressure pain threshold (PPT) will be performed in the forearm regions and tibialis anterior muscle of the dominant limbs before and after 1 min of the CPT. The tibialis anterior muscle and the distal part of the dorsal forearm, which had not been immersed in water, will be evaluated because of the lack of their relationship with the participants’ musculoskeletal complaints.

The operation of the pressure algometer and PPT measurement will be explained to the patients, and a practice test will be conducted on the patients’ dominant forearm to ensure that the test has been understood. Force will gradually be increased [1 kg-force/s] until the feeling of pressure changes to pain. The PPT will be recorded in kilograms force [Kgf]. The PPT will be repeated three times and the mean will be calculated to give the baseline PPT. The efficiency of the descending nociceptive inhibitory system will be evaluated by calculating the difference between PPT values in CPT (final cost − initial value) [41].

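### The CPM analysis names no week-12 contrast and no baseline covariate; Tukey tests on the group factor, the most direct reading, would average in the pre-treatment visit

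*Protocol article*

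**What the plan says.** All points are from the protocol article.

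- **Model** (Statistical methods for primary and secondary outcomes {20a,b}): "A repeated measure ANOVA statistic will be used to evaluate the effect of three types of exercise interventions on CPM", and on the other outcomes. The design crosses five groups, one of them the no-pain controls, with three visits: "within subjects – time: before vs. after vs. 3 months after the intervention) mixed design". The pre-treatment visit is therefore one of the outcome levels.
- **Pairwise comparisons** (same section): "Tukey’s post hoc analysis will be conducted to establish differences between the groups". No visit, change score or group-by-time contrast is attached to this test.
- **Baseline** (same section): "A one-way analysis of variance (ANOVA) will be used to compare baseline characteristics between the groups". Apart from its place as a level of the time factor, this is the only stated use of baseline. It is not a covariate for CPM.
- **Endpoint** (Outcomes {12}): "The primary efficacy endpoint will be a minimum difference of 10% change in PPT values in CPT", joined in one sentence to an NPRS criterion that runs from baseline to week 12. Secondary endpoints are changes to weeks 12 and 24. The statistical section adds that the CPM change must still be present at 6 months to count as clinically significant.
- **CPM measure** (CPM): obtained by "calculating the difference between PPT values in CPT (final cost − initial value"), that is, within one test session. The t0 value is a complete pre-treatment measurement, not a change from baseline.
- **Aim and size** (Trial design {8}; Sample size {14}): the aim is to show that one exercise group is superior to another. The size rests on an independent t-test for a difference of 80 kPa with SD 100 kPa.

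**The concern.** In a mixed ANOVA the means of the between-subject factor are averaged over all levels of the within-subject factor. Here one of the three levels is a visit at which no arm has been treated, so randomisation makes the expected difference between patient arms zero. A Tukey test on that factor estimates a diluted quantity that is neither the week-12 difference nor the 6-month difference, although the superiority claim is pairwise and Tukey is the only pairwise test offered.

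Baseline CPM is collected from everyone but is not used as a covariate, so the precision it could bring to a week-12 comparison is left unused. The risk is that a difference of the planned size is missed, or is reported at two thirds or one third of its true size.

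**Working it through.** **Inputs from the protocol (Sample size {14}).** Difference 80 kPa, SD 100 kPa, 30 per group, two-sided alpha 0.05, 87% power, 30% dropout, 43 per group.

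**Assumptions.** The between-visit correlation ρ of CPM is not given; 0.3, 0.5 and 0.7 are used, with lower values checked as well. SD is equal and correlation constant across visits.

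**Step 1: the plan's own figure.** Standard error = 100 × √(2/30) = 25.8 kPa, and 80/25.8 = 3.10. Power is 87% by the normal approximation and 86% by the noncentral t distribution. 30/0.70 = 42.9, so 43 per group. Both stated figures reproduce, but they describe a single undiluted comparison.

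**Step 2: effect under three-visit averaging.**
- Sustained (0, 80, 80): 160/3 = 53.3 kPa.
- At t1 only (0, 80, 0): 80/3 = 26.7 kPa.

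This does not depend on ρ.

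**Step 3: power of the averaged contrast without multiplicity adjustment.** SD of a three-visit mean = 100 × √((1 + 2ρ)/3). Noncentral t, 30 per group:

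| ρ | SD of mean (kPa) | Power, sustained | Power, t1 only |
|---|---|---|---|
| 0.3 | 73.0 | 79% | 29% |
| 0.5 | 81.6 | 70% | 24% |
| 0.7 | 89.4 | 62% | 21% |

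**Step 4: break-even.** For a sustained effect, averaging matches the single-visit t-test when (2/3)² = (1 + 2ρ)/3, that is ρ = (4/3 − 1)/2 = 1/6. Below this, averaging does not lose power (94% at ρ = 0, against 86%), but the estimate is still 53 kPa instead of 80.

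**Step 5: alternatives under the same Tukey correction.** Four randomised arms, 30 each: residual df = 4 × 29 = 116, critical value 2.61 on the t scale. Sustained effect of 80 kPa. SDs at week 12: 100 for the raw value, 100 × √(2(1 − ρ)) for change from baseline, 100 × √(1 − ρ²) with baseline as covariate.

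| ρ | Three-visit mean | Week 12, raw | Week 12, change | Week 12, baseline-adjusted |
|---|---|---|---|---|
| 0.3 | 59% | 69% | 51% | 74% |
| 0.5 | 47% | 69% | 69% | 83% |
| 0.7 | 39% | 69% | 92% | 96% |

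Tukey alone takes the raw week-12 contrast from 86% to 69% over four arms, and to 63% over five groups (critical value 2.76). That part of the shortfall from 87% is not caused by averaging. At ρ = 0.5 the step from 47% to 69% comes from choosing week 12, and the step from 69% to 83% from the covariate, which cuts residual variance by ρ² = 25%.

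**The case against.** **A reader might infer that the plan commits to comparing means averaged over t0, t1 and t2.** It does not say so. A five-by-three mixed design contains a group-by-time term, which baseline does not dilute, and Tukey tests at each visit would also fit "post hoc analysis will be conducted to establish differences between the groups". This stands: averaging is the most direct reading, not a stated fact. The interaction does not fill the gap, however. The plan ties no decision to it, and an omnibus test over five groups, one of them not randomised, cannot show which exercise is superior.

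**A reader might also infer that baseline is ignored.** It is not. It is a level of the time factor, and a group-by-time analysis works on within-person change. What is absent is its use as a covariate, and preferring that is a gain in precision, not the correction of an invalid method.

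**The power loss should not be overstated.** The correlations are assumed, averaging costs no power below ρ = 1/6 if the effect is sustained, and part of the shortfall belongs to Tukey. The t1-only case supposes that the effect has gone by 6 months, although participants are told to continue exercising at home. All of this stands, so the components are shown separately above.

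**The endpoint is itself loosely worded.** The week-12 timing is attached grammatically to the NPRS, and "Secondary endpoints include change from baseline to weeks 12 and 24" concerns other measures. This is fair, but the three-visit mean matches neither the week-12 nor the 6-month reading.

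**Such detail is often left to an analysis plan.** That would answer a complaint about silence. Here the article states the model, its visit levels and its post hoc test, and these do not lead to the comparison that the aim requires.

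**Conclusion.** The point holds in a limited form. The article specifies a model with the pre-treatment visit as an outcome level and one pairwise procedure not tied to any visit, and it uses no baseline covariate. On the most direct reading, the group comparison shrinks a sustained 80 kPa difference by one third and a t1-only difference by two thirds, whatever the correlation. The accompanying loss of power depends on assumed correlations: without multiplicity adjustment it falls from the planned 87% to between 79% and 62% for ρ from 0.3 to 0.7, with no loss below about 1/6 if the effect lasts.

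Under a common Tukey correction over the four randomised arms, a baseline-adjusted week-12 contrast beats the averaged, raw and change-score contrasts at each of these correlations. The documents do not support calling the planned analysis invalid, since readings without the dilution remain open. It should be fixed because the contrast that carries the superiority claim is left to interpretation.

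**What to change.** In {20a,b}, replace the repeated-measures ANOVA and Tukey sentences for CPM with wording to this effect: the primary contrasts are the pairwise differences in CPM at week 12 among the four randomised arms, estimated from a mixed model for t1 and t2 (or an ANCOVA) with arm, visit, arm-by-visit interaction and baseline CPM, with Tukey-type adjustment over those arms. The 6-month contrasts come from the same model. The no-pain group is compared separately, outside the randomised comparison.

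A centre term is optional and not part of this point.

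The cost is a change of analysis wording. Baseline CPM is already collected, so no new data or visits are needed, and a standard mixed-model procedure is enough. The sample size section should then describe the power of this contrast and state the between-visit correlation assumed.
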